### Hypothesis and objectives

1.2

Based on the published literature, we assume that allopathic and Ayurvedic treatments are equally effective in treating depression, both leading to improvements in symptom severity. Therefore, we do not expect any statistically significant difference in treatment effect between the treatment groups (between-group effect) in week 8. However, we hypothesize that both therapies will lead to an improvement in depression symptoms over a period of 8 weeks (within-group effect). The question is exploratory in nature due to the design and methodology.

This study will pursue the following scientific objectives:

Treatment Effect: To quantitatively compare the effect of allopathic and ayurvedic treatments (and their combination) in reducing the severity of depressive symptoms in MDD, as measured by validated rating scales (primary Montgomery-Åsberg Depression Rating Scale (MADRS), secondary Hamilton Depression Rating Scale (HAM-D) and Patient Health Questionnaire-9 (PHQ-9) at baseline, 8 weeks, 3 months and 6 months.Side Effects and Quality of Life: To compare the incidence, type, and severity of adverse events associated with allopathic and ayurvedic treatments using standardized adverse event reporting like Udvalg for Kliniske Undersøgelser Scale (UKU), General Assessment of Side (GASE) and Medication Adherence Report Scale (MARS). Furthermore, to assess differences in quality of life (QoL) and daily functioning between treatment groups using validated QoL instruments (e.g., WHOQOL-BREF) and functional assessment scales (e.g., Global Assessment of Functioning (e.g., Global Assessment of Functioning (GAF) and Functional Assessment Short Test (FAST).General Health Evaluation: To evaluate and compare changes in general health parameters (e.g., Body Mass Index (BMI), vital signs, relevant blood work indicators such as liver and kidney function tests, electrolytes, CRP, leukocytes, red blood cells, platelets, haemoglobin , haematocrit , red cell indices and TSH) across treatment groups over the study duration.

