### Primary and secondary outcome measures

2.7

The primary endpoint will focus on changes in depressive symptom severity, measured using primary MADRS, and secondary HAM-D and PHQ-9 especially in week 8. The use of multiple scales enhances the reliability and validity of the assessment, providing a more comprehensive picture of symptom change. Several secondary outcome measures will exploratively elucidate the impact of treatments on various aspects of patient well-being and functioning. These include side effects (UKU, GASE, MARS), quality of life and daily functioning (WHOQoL-BREF, GAF, FAST) as well as general health measures (e.g. lab tests). This comprehensive approach ensures that the study captures a broad range of outcomes, providing a robust and nuanced evaluation of the treatment effect and side effects of allopathic and Ayurvedic treatments for MDD. The question is exploratory in nature due to the design and methodology.

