The choice of statistical test will depend on the nature of the data and the specific research question. For continuous outcome variables (e.g., scores on depression rating scales, quality of life scores, continuous physiological measures), Analysis of Variance (ANOVA) or independent samples t-tests will be used to compare means between the three treatment groups (Ayurvedic-only, Allopathic-only, and Combination). *Post-hoc* tests (e.g., Tukey’s HSD, Bonferroni correction) will be employed if significant differences are found between groups to determine which specific groups differ significantly. For categorical outcome variables (e.g., presence or absence of adverse events, categorical measures of quality of life, treatment adherence categories), Chi-square tests or Fisher’s exact tests (for small sample sizes) will be used to compare proportions between treatment groups. Given the repeated measures design (baseline, 8 weeks, 3 months, 6 months), appropriate statistical models for longitudinal data (e.g., repeated measures ANOVA, mixed-effects models) will be used to analyse changes in outcome measures over time within each treatment group and to examine the interaction effects between treatment group and time. This will allow for a more powerful examination of treatment effects and the assessment of treatment response trajectories. Strategies to address missing data will be carefully considered and documented. In addition to p-values, effect sizes (e.g., Cohen’s d) and 95% confidence intervals will be reported for all significant findings. All statistical analyses will be performed using appropriate statistical software packages (e.g., SPSS, R).

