## Conclusions

4

With its comprehensive, methodologically sound, and realistic design, this study is positioned to generate valuable real-world evidence in a still young field of research. Rather than providing definitive clinical recommendations, the findings will serve as hypothesis-generating data on the potential effects of a holistic Ayurvedic approach, either alone or in combination with allopathic treatments, for individuals with depression. The results are expected to inform the design of future randomized controlled trials (RCTs) and highlight promising integrative strategies. In doing so, this study will stimulate further systematic investigation and contribute to the growing body of knowledge on integrative and complementary psychiatry.

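### Effect sizes and 95% confidence intervals are promised only for significant findings, so the between-arm results most likely to be null carry no promised estimate

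*Protocol article*

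**What the plan says.** All of this is in the protocol article.

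- **Reporting rule (section 2.9).** Beside p-values, effect sizes and "95% confidence intervals will be reported for all significant findings". No other sentence in the article commits to effect sizes or intervals.
- **Second condition (section 2.9).** Post-hoc tests "will be employed if significant differences are found between groups to determine which specific groups differ significantly".
- **Expected result (section 1.2).** For the depression outcome at week 8, "we do not expect any statistically significant difference in treatment effect between the treatment groups". Section 2.9 repeats the hypothesis that the groups do not differ in treatment success.
- **Objectives (section 1.2).** One objective is "To compare the incidence, type, and severity of adverse events associated with allopathic and ayurvedic treatments". Another is to compare BMI, vital signs and blood work across the groups.
- **Size (section 2.1).** There are three groups of approximately 35, 105 in all.
- **Purpose (sections 1.2, 2.7 and 4).** The question is called exploratory, and the results are meant to generate hypotheses and feed into the design of later randomized trials.

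**The concern.** The rule attaches the estimate and its precision to the results that cross a significance threshold. For the between-arm comparison of depression, the authors say they expect the opposite outcome. For side effects and general health they state no such expectation, but with about 35 per arm a difference of moderate size will often miss significance.

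Two things are at stake. First, section 1.2 starts from the assumption that the treatments work equally well. A p-value above 0.05 cannot support that, because it does not show which differences the data still allow. The same holds for safety, where a non-significant comparison can be taken for reassurance. Second, effect sizes shown only for significant comparisons are too large on average, which matters for a study whose results are to inform later trials.

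**Working it through.** **Inputs.** From the article: 35 per arm (section 2.1) and the 95% level (section 2.9). Assumed: two-sided 0.05, because section 2.9 prints the alpha as 0.5; equal variances and normal data; and the true between-arm differences and event counts used below.

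**The plan's own power figure.** Section 2.9 claims power above 0.8 at an effect size of 0.5 and names no test. A paired t-test within one arm of 35 gives 0.820 at two-sided 0.05 (0.989 at the printed alpha), so the claim reproduces as a within-arm statement. A two-sample t-test of 35 versus 35 at d = 0.5 has power 0.541. The power claim read in this way does not carry over to a comparison of two arms.

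**Interval width, continuous outcome.** Half-width in SD units = t(0.975, 2n - 2) × √(2/n).

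- n = 35: 1.9955 × 0.2390 = 0.477
- n = 30: 0.517; n = 25: 0.569
- Tukey adjustment at n = 35: 0.569
- Baseline adjustment, assumed correlation 0.5: 0.477 × √(1 - 0.25) = 0.413

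The article gives no SD for MADRS. If it is 8 to 12 points, the unadjusted half-width at 35 per arm is 0.477 × 8 = 3.8 to 0.477 × 12 = 5.7 points.

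**Interval width, binary outcome.** The SD figure does not apply here. With 1.96 × √(2p(1 - p)/35), the half-width is about 14 points at an assumed rate of 10%, 21 at 30% and 23 at 50%.

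Illustration with 14/35 versus 7/35 (40% versus 20%):

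- Fisher p = 0.117.
- Wilson limits: 25.6% to 56.4%, and 10.0% to 35.9%.
- Newcombe lower limit: 20.0 - √(14.4² + 15.9²) = -1.5 points.
- Newcombe upper limit: 20.0 + √(16.4² + 10.0²) = 39.2 points.

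**How often no interval is promised.** Share = 1 - power. Two-arm power comes from the noncentral t with 68 df and noncentrality d × √(35/2). For the three-arm ANOVA, d is the difference between the extreme arms, with the third arm midway.

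| Assumed true d | Two-arm power | Two-arm, not significant | Three-arm ANOVA, not significant |
|---|---|---|---|
| 0 | 0.05 | 95% | 95% |
| 0.2 | 0.131 | 87% | 90% |
| 0.3 | 0.236 | 76% | 82% |
| 0.5 | 0.541 | 46% | 56% |

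**Inflation among significant results.** At 35 per arm a two-arm difference is significant only if the observed |d| is at least 0.477. Over 400,000 simulated trials per setting, the mean |d| among significant results was 0.60, 0.62 and 0.69 when the truth was 0.2, 0.3 and 0.5.

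**The case against.** The strongest reply is that the sentence sets a minimum: it does not say that intervals will be given for significant findings alone, and tabulation is usually left to the full protocol or analysis plan. A reader might infer that the study will withhold all other intervals. The article does not say that, and the unseen documents may add them. What stands against the reply is that the article chose to print a condition on significance and nowhere widens it. The point is about that printed rule.

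Other parts of the case against hold, and they limit the point:

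- A reader might apply 0.48 SD to every comparison. It fits only an unadjusted difference in means at full enrolment. Presence or absence of an adverse event is categorical, and dropout, multiplicity correction or baseline adjustment changes the width.
- A reader might extend the expectation of no difference to safety and laboratory values. The article states it for depression only. Elsewhere, frequent non-significance would follow from small samples if the true differences are modest.
- A reader might take section 2.9's effect size of 0.5 as a between-arm effect. It is described there as a change from baseline to week 8, so every non-zero between-arm d above is an assumption.
- Null results would not be useless to a trial planner. If means, SDs or event counts are published, intervals can be rebuilt from them, and nothing says these will be withheld.
- Improvement within each arm is expected to be significant and, if so, would receive intervals under the present rule.
- Gating post-hoc p-values on an overall test is conventional. The problem is only that no pairwise estimate is promised when the gate stays shut.

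**Conclusion.** The point holds for between-arm comparisons. As printed, the rule promises no effect size or interval for the between-arm depression result that the authors expect, nor for any safety or general health comparison that misses significance. The uncertainty left unshown is material: about 0.48 SD either way for an unadjusted mean difference at 35 per arm, and up to 39.2 points in the illustrative adverse-event comparison. Under assumed true differences of d = 0.2 to 0.5, 87% to 46% of two-arm comparisons would fall outside the promise, and those inside it would average 0.60 to 0.69.

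These shares rest on two-sided 0.05, full enrolment, unadjusted tests and d values that the document does not supply. The direction of the argument does not depend on them. The study's exploratory status makes estimates more useful, so it does not excuse the rule. This should be changed because it is cheap; it is no fatal flaw.

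**What to change.** In section 2.9, replace the closing condition of the reporting sentence so that effect sizes and 95% confidence intervals are given *for all between-group comparisons (each pair of groups) and all within-group comparisons, whether or not significant*. Label these intervals as descriptive and unadjusted for multiplicity. Post-hoc p-values may stay conditional on the overall test; the pairwise estimates should not be.

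The cost is one phrase in the text and longer tables from data already being collected. No visits, samples or patients are added. The gain is visible precision and a complete set of estimates; power does not change.

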## Discussion

3

Even though there are well-established and scientifically sound treatment approaches for depression, 30% of treatment cases are considered resistant to therapy (37, 38). These prevalence rates are worrying. There is an enormous need for alternative, low-side-effect, and effective complementary treatments for depression. Complementary and alternative medicine is widespread and established in both industrialized and developing countries. Up to 65% of people in industrialized countries and 80% of people in developing countries use it for psychosomatic complaints such as depression [42,43]. Studies that scientifically investigate complementary or alternative treatments focus predominantly on individual interventions, whereas Ayurveda is designed as a holistic treatment approach, which is a dominant feature of the study design (39).

### Strengths

3.1

The study design we have developed provides an opportunity to evaluate allopathic, Ayurvedic, and combined therapeutic approaches in a real-world setting. The study also highlights the potential of integration of Ayurvedic and allopathic approaches as innovative approaches with real-world generalizability. The study is designed as a longitudinal study with a follow-up period of six months so that long-term effects can also be exploratively investigated. The study includes extensive clinical and somatic examinations, self-reports, and interviews so that both objective and subjective assessments can be considered. The design allows individualized and adaptive treatment of patients.

The problem of ergodicity (40)—that interindividual differences do not necessarily reflect intraindividual dynamics and that conclusions based on group-level data cannot be directly transferred to individual patients—plays a role in the interpretation of our findings. We explicitly use group-level results as evidence of average treatment effects and will use them as a starting point for individualized care. We operationalize this through measurement-based monitoring, stepwise treatment adaptation, and—where feasible—idiographic designs (e.g., intensive longitudinal assessments, single-case or N-of-1 approaches) to evaluate within-person responses and further optimize treatment for the individual patient.

The study thus offers high ecological validity and the potential to be transferable to everyday clinical practice . At the same time, the collection of routine blood markers and vital parameters offers a opportunity to gain exploratively neurobiological insights. The multi-professional team and international collaboration offer the advantage of combining in-depth expertise in various fields.

### Limitations

3.2

While the real-world study has advantages for translation and generalizability to clinical practice , this comes with limitations such as potential confounding, selection bias, and heterogeneity of Ayurvedic and allopathic interventions, which could affect internal validity. In this context, it should be noted that the choice of treatment depends strongly on the preferences of the patients and the approach of the treating clinic and physicians, even though participatory decision-making processes are particularly important with regard to the treatment of psychiatric patients. Even though a wait-list control condition or a no-intervention arm would provide valuable data and improve the interpretability of the findings, this would not be ethically justifiable in our sample.

Moreover, the generalizability is limited to comparable settings in India. It should be noted that the exclusion of suicidality and substance abuse leads to a small but ethically necessary restriction of the naturalistic cohort.

Furthermore, the approach of a multimodal and routine (non-randomised) intervention program in both Ayurvedic and allopathic treatment arms have the potential disadvantage that no causal inferences can be made about specific effects of individual components of the treatment. However, we would like to emphasize that a more holistic approach to treating depression reflects clinical reality and carries a higher weight for translation into routine settings.

This study is designed to determine whether the applied treatments are effective in producing changes in the dependent variables. However, it is not intended to explain how or through which mechanisms the treatment leads to successful outcomes. Addressing this question would require a research design that captures the complexity of real-world settings with greater ecological validity (e.g., alternative approaches such as the integrative single-case design) (41).

## Conclusions

4

With its comprehensive, methodologically sound, and realistic design, this study is positioned to generate valuable real-world evidence in a still young field of research. Rather than providing definitive clinical recommendations, the findings will serve as hypothesis-generating data on the potential effects of a holistic Ayurvedic approach, either alone or in combination with allopathic treatments, for individuals with depression. The results are expected to inform the design of future randomized controlled trials (RCTs) and highlight promising integrative strategies. In doing so, this study will stimulate further systematic investigation and contribute to the growing body of knowledge on integrative and complementary psychiatry.
